#### Secondary Outcomes (Efficacy Assessment)

The efficacy of the treatment is functional independence which will be assessed by the modified Rankin Scale (mRS, mRS scores of 0 to 2 indicating functional independence), and infarct volume as well as NIHSS scores. MRI will be performed at baseline and on days 3 and 90. We will measure the infarct volume on a Siemens Syngo with T1, T2, T2-flair, Diffusion-Weighted Imaging (DWI), Arterial Spin Labeling (ASL) and Intra-Voxel Incoherent Motion (IVIM). We will calculate the infarct volume by using the image tool (ROI) on the workstation to outline the lesion on each slice to compute the area, and multiply the area of each layer by the thickness of each layer.

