### Estimation of Sample Size

There is no data available for reference because no completed clinical study of C+P in AIS patients without EVT currently exists. However, Hertzog has suggested that 10 to 20 patients in each group are sufficient to assess the feasibility of a pilot study (22) while Dobkin has shown that 15 patients in each group is usually enough to decide whether a larger multicenter trial should be conducted (23). Therefore, our goal is to recruit 15 patients in each group, a similar number of samples was selected for another protocol (24). The results of this study should be able to determine the initial safety and feasibility of intravenous infusion of C+P in AIS patients. The data will be used to estimate sample size and conduct a power calculation to plan a phase-2 trial for efficacy.

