### Statistical Analyses

The endpoint event analysis is based on the intention-to-treat (ITT) principle, including all randomly enrolled subjects. If compared to the control group, the treatment group did not have an increase in the incidence of adverse reactions and there was no difference in 90 days prognosis between the two groups, we would move forward with a phase-2 trial.

Categorical variables including the proportion of good functional outcomes and the frequency of adverse events will be presented as counts and percentages. χ^2^-test, Fisher exact-test, or continuity correction will be used where appropriate for comparison between the two groups. If the continuous variables including NIHSS score and infarct volume conform to the normal distribution, it shall be indicated by mean ± standard, and tested by *t*-test, and if it does not conform to the normal distribution, it shall be indicated by median and interquartile range and tested by Mann-Whitney *U*-test. *p* < 0.05 will be considered statistically significant. SPSS 22.0 software will be used for statistical analysis.

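### The mRS is compared only as 0-2 versus 3-6; a full-scale analysis of the same data would give a more precise pilot estimate

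*Protocol article*

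**What the plan says.** Under Secondary Outcomes (Efficacy Assessment), the protocol article lists mRS, infarct volume and NIHSS as efficacy measures. It reads the mRS through one cut: "mRS scores of 0 to 2 indicating functional independence".

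Statistical Analyses treats the result as categorical: "Categorical variables including the proportion of good functional outcomes and the frequency of adverse events will be presented as counts and percentages". The tests are chi-square or one of two alternatives: "Fisher exact-test, or continuity correction will be used where appropriate for comparison between the two groups". The other efficacy measures are not cut: "If the continuous variables including NIHSS score and infarct volume conform to the normal distribution" they get a t-test, and otherwise a Mann-Whitney test.

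The same section sets the condition for going on. Besides no increase in adverse reactions, it requires that "there was no difference in 90 days prognosis between the two groups, we would move forward with a phase-2 trial". It does not say which endpoint carries prognosis. Study Design schedules mRS, NIHSS and MRI at day 90.

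On size, Estimation of Sample Size says "our goal is to recruit 15 patients in each group". It gives no power, effect size or control rate, and says the data will be used to plan a phase-2 trial.

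**The concern.** The mRS has seven ordered levels. Cutting it between 2 and 3 discards every movement within 0-2 and within 3-6; a shift from 3 to 5, for example, leaves the comparison unchanged. If treatment moves patients across the whole scale, the two-by-two test is less sensitive and the effect estimate less precise than the collected data allow.

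Two uses are at stake. The pilot is meant to inform the phase-2 sample size, so a noisier estimate is a poorer planning input. And a finding of no difference at 90 days counts towards proceeding, so if prognosis is judged on the cut mRS, an insensitive test leans towards proceeding.

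**Working it through.** **No figure to reproduce.** The sample size rests on pilot rules of thumb. The check therefore asks what the cut costs at that size.

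**Inputs from the protocol article.** 15 per arm (the 30 in Randomization and Blindness is read as the total); 1:1 allocation; significance level 0.05; cut at 0-2 versus 3-6; chi-square, Fisher or continuity correction.

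**Assumptions.** Two-sided testing; a proportional-odds shift; four control distributions over mRS 0 to 6:
- 25% at 0-2: .03, .09, .13, .18, .25, .14, .18
- 35%: .06, .13, .16, .18, .22, .10, .15
- 50%: .12, .20, .18, .16, .16, .08, .10
- 60%: .18, .24, .18, .14, .12, .06, .08

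**Step 1: information kept by the cut.** For small proportional-odds effects, relative efficiency = 3p(1-p) / (1 - Σp_k³), where p is the proportion at 0-2 and p_k the seven level probabilities. At 35%: 3 × 0.35 × 0.65 = 0.6825; Σp_k³ = 0.0274; 0.6825 / 0.9726 = 0.70. The other rates give 0.58 (25%), 0.77 (50%) and 0.74 (60%). The loss is thus 23% to 42%.

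A fifth assumed distribution (.06, .14, .16, .16, .18, .12, .18; 36% at 0-2) shows the same as variances of the log odds ratio. Binary: 2 / (15 × 0.36 × 0.64) = 0.579. Ordinal: 12 / (30 × (1 - 0.0245)) = 0.410. Ratio 1.41.

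**Step 2: power at 15 per arm.** 20,000 simulated trials per cell; entries are Mann-Whitney / uncorrected chi-square / Fisher, in %. An odds ratio (OR) above 1 is benefit.

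| Control 0-2 | OR 2 | OR 3 | OR 5 | OR 1/2 | OR 1/3 |
|---|---|---|---|---|---|
| 25% | 17.7 / 14.3 / 6.2 | 37.6 / 29.5 / 15.7 | 67.0 / 55.3 / 38.0 | 18.1 / 11.6 / 4.8 | 36.6 / 17.2 / 8.4 |
| 35% | 17.5 / 14.1 / 6.7 | 37.7 / 29.9 / 17.7 | 66.4 / 55.1 / 38.6 | 18.3 / 14.3 / 6.0 | 37.3 / 24.8 / 12.5 |
| 50% | 18.1 / 14.4 / 7.0 | 37.3 / 28.9 / 15.4 | 65.9 / 51.1 / 32.4 | 18.4 / 14.9 / 7.1 | 37.1 / 29.2 / 15.8 |
| 60% | 17.8 / 14.5 / 6.0 | 36.3 / 27.1 / 13.6 | 65.2 / 45.7 / 27.5 | 17.7 / 14.6 / 7.3 | 37.6 / 30.1 / 17.7 |

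Relative loss = 1 - (power of the cut / power of Mann-Whitney). For benefit:
- Chi-square: 17% (1 - 55.1/66.4) to 23% (1 - 28.9/37.3) at control rates of 25-50%, and up to 30% at 60% (1 - 45.7/65.2).
- Fisher: 42% (1 - 38.6/66.4) to 66% (1 - 6.0/17.8).

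Much of the Fisher loss is its own conservatism. Its actual size here is about 1.5-1.9%, against about 5% for Mann-Whitney and chi-square.

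**Step 3: which two-by-two test would be used.** The article leaves this to appropriateness. Assume the common rule: Fisher if any expected count is below 5, otherwise chi-square. At a control rate of 36%:
- Benefit (OR 2 to 4): expected counts reach 5 in 92-96% of tables, so chi-square is usual and the loss is about a fifth to a quarter.
- Harm: good outcomes become rarer and Fisher is triggered in 64-85% of trials. Power by Mann-Whitney versus the rule is 17% v 8% (OR 1/2), 37% v 16% (OR 1/3) and 52% v 22% (OR 1/4).

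For harm at OR 1/3, the other rates give 36% v 9% (control 25%, a loss of 75%) and 36% v 25% (control 50%, a loss of 31%).

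An illustration that needs no distribution: with 5 of 15 controls independent, Fisher reaches p < 0.05 for harm only at 0 of 15 treated (p = 0.042); 1 of 15 gives p = 0.17.

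**Step 4: a shift that favours the cut.** Control 35%, 15 percentage points moved from mRS 3 to mRS 2: chi-square 12.8%, Fisher 5.6%, Mann-Whitney 5.7%.

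**The case against.** A reader might infer that dichotomising throws away half the power of the very comparison that decides on phase 2. The documents do not support that, for four reasons.

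- **Half is not a property of the cut.** It appears against Fisher or the continuity correction, or for harm at lower control rates. Uncorrected chi-square loses about a fifth for benefit in most scenarios.
- **The direction depends on the effect.** No reference data exist, as the article says, and a shift concentrated between 2 and 3 reverses the ranking.
- **The go rule is not tied to mRS 0-2.** It speaks of 90-day prognosis only. NIHSS and MRI are also taken at day 90, and NIHSS and infarct volume keep their full scale. The link is plausible, not stated.
- **Deaths are not hidden.** All-cause death is a separate safety outcome under Primary Outcomes (Safety Assessment), and adverse-event frequencies are compared between groups.

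It can also be said that this is an unpowered pilot with hypotension as its main outcome, that functional independence is a legitimate measure which phase 2 may keep, and that a supplementary ordinal analysis could sit in a plan not shown. These points stand and limit the importance. They do not remove the point: the article states how the mRS is compared, and a more informative analysis of the same data needs only a test already in the plan.

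**Conclusion.** The point holds as a cheap improvement to a secondary analysis. Its size is the 23-42% information loss of step 1 and the test-dependent power losses of steps 2 and 3. All of these rest on assumed control distributions and, step 4 apart, on a proportional-odds shift; none is a figure from the article.

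The gain is a more precise pilot estimate, not a repaired decision rule. At OR 2 or 1/2, power is at or below about 18% with any of these tests, so more than 80% of such trials would still show no significant difference. Near 50%, the 95% CI for a difference in proportions has a half-width of 1.96 × √(2 × 0.25 / 15) = 0.36, or 36 points. Reading non-significance as reassurance, with no margin, is a separate weakness that an ordinal test does not cure.

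**What to change.** In Statistical Analyses, state that day-90 mRS will be compared on the full 0-6 scale, with death scored 6, by Mann-Whitney or by a proportional-odds model giving a common odds ratio with 95% CI. Report the 0-2 proportion by arm, with the CI of the difference, alongside it.

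The cost is about one sentence. It needs no extra patients or visits, since mRS is already scored at day 90. The downside is that a common odds ratio is less familiar than a proportion and assumes proportional odds. Keeping the 0-2 proportion preserves the planning input if phase 2 retains that endpoint.

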### Estimation of Sample Size

There is no data available for reference because no completed clinical study of C+P in AIS patients without EVT currently exists. However, Hertzog has suggested that 10 to 20 patients in each group are sufficient to assess the feasibility of a pilot study (22) while Dobkin has shown that 15 patients in each group is usually enough to decide whether a larger multicenter trial should be conducted (23). Therefore, our goal is to recruit 15 patients in each group, a similar number of samples was selected for another protocol (24). The results of this study should be able to determine the initial safety and feasibility of intravenous infusion of C+P in AIS patients. The data will be used to estimate sample size and conduct a power calculation to plan a phase-2 trial for efficacy.

### Statistical Analyses

The endpoint event analysis is based on the intention-to-treat (ITT) principle, including all randomly enrolled subjects. If compared to the control group, the treatment group did not have an increase in the incidence of adverse reactions and there was no difference in 90 days prognosis between the two groups, we would move forward with a phase-2 trial.

Categorical variables including the proportion of good functional outcomes and the frequency of adverse events will be presented as counts and percentages. χ^2^-test, Fisher exact-test, or continuity correction will be used where appropriate for comparison between the two groups. If the continuous variables including NIHSS score and infarct volume conform to the normal distribution, it shall be indicated by mean ± standard, and tested by *t*-test, and if it does not conform to the normal distribution, it shall be indicated by median and interquartile range and tested by Mann-Whitney *U*-test. *p* < 0.05 will be considered statistically significant. SPSS 22.0 software will be used for statistical analysis.

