### Randomization and Blindness

During the recruitment period, participants will be allocated 1:1 to two groups (*n* = 30) by computer-generated randomization procedures using opaque envelopes. A research assistant not involved in the study will prepare the envelopes before the study. After recording baselines measures, participants will be randomly allocated to either the intervention or the control group by the treating physicians who will open the sealed opaque envelopes. In order to minimize selection bias, patients and assessors involved in the trial will be masked to treatment allocation. All outcome measurements will be assessed by two observers blinded to the treatment plan, any disagreement will be resolved by reaching a consensus between the two. If no consensus can be reached, a third observer blinded to the treatment assignment and not involved in the clinical treatment plan will have a final decision. Finally, an independent investigator blinded to the treatment assignment will collect the data of outcomes and information of the group, and analyze them.

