### Outcomes

#### Primary Outcomes (Safety Assessment)

The main safety parameter is the incidence of hypotension requiring clinical intervention (≤90/60 mmHg). The secondary safety outcomes are the occurrence of adverse events including (1) neurologic deterioration defined as an increase of four or more points in the NIHSS within 7 days without clear explanation; (2) death during the study period regardless of cause; (3) body temperature down to below 36°C; (4) severe arrhythmias, such as sick sinus syndrome, rapid atrial fibrillation, supraventricular tachycardia, etc., which may cause palpitations, chest tightness, dizziness and other clinical manifestations; (5) liver damage: alanine aminotransferase (ALT) and aspartate aminotransferase (AST) concentrations were doubled; (6) seizures: epilepsy occurs within 2 weeks of stroke; (7) extrapyramidal responses (tremor, rigidity, salivation, and bradykinesia).

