The RICHES study is designed to identify the safety, feasibility, and secondarily any possible efficacy of intravenous administration of C+P in AIS patients. The preliminary results will provide clues for the design of future clinical trials. If there is no significant difference in the incidence of drug-related adverse events between the experimental group and the control group, further clinical trials will be indicated. Based on past basic research and previous clinical studies, we predict that chlorpromazine and promethazine is safe for patients with acute ischemic stroke. The current study may suggest a neuroprotective role in AIS, and warrant a randomized controlled trial (RCT).

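### Intention to treat is the only analysis set stated for the hypotension outcome; because finding no increase lets the trial proceed, patients who never start C+P dilute harm and favour proceeding.

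*Protocol article*

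**What the plan says.** The Statistical Analyses section of the protocol article names one analysis set: "The endpoint event analysis is based on the intention-to-treat (ITT) principle, including all randomly enrolled subjects". It names no separate set for safety.

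The Primary Outcomes section makes safety the primary question: "The main safety parameter is the incidence of hypotension requiring clinical intervention", with a threshold of 90/60 mmHg or below. A list of other adverse events follows as secondary safety outcomes.

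The rule for going on to phase 2 comes directly after the intention-to-treat sentence. Its safety part is that "the treatment group did not have an increase in the incidence of adverse reactions"; its other part is that 90-day prognosis does not differ. The Discussion words the safety part as a significance criterion: "If there is no significant difference in the incidence of drug-related adverse events between the experimental group and the control group", further trials are indicated.

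The Estimation of Sample Size section says "our goal is to recruit 15 patients in each group". Under Randomization and Blindness, treating physicians open the envelopes once baseline measures are recorded, so allocation comes before the infusion. Study Design adds that C+P follows rt-PA in patients who receive thrombolysis. Under Interventions, controls receive a saline infusion.

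**The concern.** Intention to treat is the cautious choice when a trial has to show a difference, because departures from allocation pull the arms together. Here the safety decision is favourable when no difference is seen, so the same pull works in favour of proceeding. A patient allocated to C+P who never receives it carries only the background risk of hypotension but still counts in the C+P denominator.

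The text leaves room for this. Allocation precedes the infusion, thrombolysed patients get C+P only after rt-PA, and the inclusion criterion limits the time from onset to treatment, not to randomisation. At stake is the estimate of harm on which the phase 2 decision rests, in a trial too small to absorb much dilution. The Discussion already predicts that the combination is safe, so the dilution runs towards the expected answer.

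**Working it through.** **Plan's own figure.** The 15 per group comes from pilot-study rules of thumb, with no event rate, margin or power, so there is no calculation to reproduce.

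**Inputs from the article.** n = 15 per arm, allocation 1:1, Fisher's exact test among the tests named for event frequencies, and a 0.05 level ("0.05 will be considered statistically significant"). Sidedness is not stated; two-sided is assumed.

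**Assumptions.** Background hypotension risk pC = 5%; risk in patients who start C+P pT = 20%, 30% or 40%; k = 0 to 3 of the 15 allocated to C+P never start and carry the background risk. The article gives none of these. Control non-starters do not alter the intention-to-treat result, because saline and no infusion are assumed to carry the same risk.

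**Step 1: dilution of the excess.** Expected C+P rate under intention to treat = [(15−k)·pT + k·pC]/15. Subtracting pC gives an expected excess of (pT−pC)·(15−k)/15. The factor is 14/15 = 93%, 13/15 = 87% and 12/15 = 80% for k = 1, 2, 3, whatever the event rates. Example: 5% v 40% with k = 2 gives (13×0.40 + 2×0.05)/15 = 5.3/15 = 35.3%, an excess of 30.3 points where the true excess is 35.

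**Step 2: effect on the decision.** Events in the C+P arm are the sum of Binomial(15−k, pT) and Binomial(k, pC); control events are Binomial(15, pC). Harm is flagged when the C+P count is higher and two-sided Fisher p < 0.05. With 15 per arm this needs at least 5 v 0 (p = 0.042) or 7 v 1 (p = 0.035). Adding the probabilities of all such outcomes gives the chance of flagging harm (the Discussion's wording). Adding those with C+P count ≤ control count gives the chance of seeing no numerical increase (the Statistical Analyses wording, read literally).

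| Assumed rates | Result under intention to treat | k = 0 | k = 1 | k = 2 | k = 3 |
|---|---|---|---|---|---|
| 5% v 40% | harm flagged | 52% | 46% | 40% | 35% |
| 5% v 30% | harm flagged | 27.5% | 23.6% | 19.8% | 16.3% |
| 5% v 30% | no numerical increase | 4.4% | 5.4% | 6.7% | 8.2% |
| 5% v 20% | harm flagged | 8.3% | 6.9% | 5.7% | 4.6% |
| 5% v 20% | no numerical increase | 15.6% | 17.3% | 19.3% | 21.5% |

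Under both wordings of the rule, each non-starter moves the result towards proceeding.

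**Step 3: what a treated-set analysis recovers.** Among starters the full expected excess is restored, but the sample is smaller. If non-starts are equal in the two arms, the chance of flagging harm at 5% v 40% is 48%, 42% and 36% for k = 1, 2, 3, against 46%, 40% and 35% under intention to treat. At 5% v 30% it is 24.0%, 20.1% and 16.3%, against 23.6%, 19.8% and 16.3%. The gain is an undiluted estimate; almost no power is won back.

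**The case against.** **Non-starters are conjecture.** The article gives no non-start rate. It does not say that randomisation precedes the end of rt-PA, or that a randomised patient who later crosses an entry limit goes untreated. With a single infusion after allocation, k may well be zero, and then the two sets coincide. This stands: the finding is conditional.

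**A reader might infer that one non-starter reverses the decision.** Four events in 14 treated against 0 in 15 give p = 0.042, while 4/15 v 0/15 gives p = 0.100. But 4/14 v 0/14 gives p = 0.098, so the apparent reversal comes from how the discrete Fisher test behaves with unequal arms. Read literally, the Statistical Analyses wording counts 4 v 0 as an increase in either set. For the same reason, the treated set should not be credited with a large gain in power: with 14 v 15 patients at 5% v 40% the computed figure is 62%, above the 52% for a full 15 v 15.

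**A reader might also take the endpoint to be drug-induced hypotension,** so that non-starters could not have an event. The article counts any hypotension requiring intervention, which is why non-starters are given the background risk above.

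**The treated set can be biased.** Treating physicians open the envelopes, and only patients and assessors are stated to be masked. If a physician who knows the allocation withholds C+P from patients with falling blood pressure but still runs saline in such patients, the treated C+P group loses those most prone to hypotension, which also favours proceeding. This stands, and it is why intention to treat should not simply be replaced.

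**A safety population is often left to the SAP.** That is true, and silence would be no finding. But the article is not silent: it gives one set for endpoint events without exception, and the primary endpoint is a safety event.

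**Conclusion.** The point holds, at modest size. The stated analysis set is not conservative for a safety outcome whose favourable result is the absence of an increase. Each non-starter among 15 takes about 7% off the expected excess (1/15). For one to three non-starters, the chance of flagging harm drops by 6 to 17 percentage points at an assumed 5% v 40%, and by 4 to 11 points at 5% v 30%. These sizes rest on assumed event rates, on non-starters carrying the background risk, and on k, for which the article gives no value.

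The documents do not show that non-starts will occur, or that the sponsor's decision would be reversed by one. Low power at 15 per arm is the larger weakness: even with every patient treated, an excess of 5% v 30% is flagged only 27.5% of the time, and changing the analysis set does not cure that.

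**What to change.** In Statistical Analyses, restrict the intention-to-treat sentence to mRS, NIHSS and infarct volume. For hypotension and the other adverse events, state that:

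- the analysis includes patients who started any study infusion, C+P or saline, grouped by what they received, and the adverse-event part of the progression rule is based on that set;
- the intention-to-treat safety result is reported beside it, with the number of non-starts and the reasons by arm;
- an increase in either set counts against proceeding.

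The last condition covers both biases: dilution under intention to treat, and selective withholding in the treated set. The Discussion's version of the rule should be brought into line.

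The cost is a few sentences and one extra table, with no new data beyond recording whether the infusion was started and, if not, why. The downside is that the treated set is not strictly the randomised comparison, which is why both are shown. If every patient starts the allocated infusion, the two analyses are identical and nothing is lost.

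### The article states two different go rules for the primary safety question, and neither supports a safety decision with 15 patients per arm

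*Protocol article*

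**What the plan says.** Safety is the primary outcome, and its main parameter is hypotension requiring clinical intervention (Protocol article, Primary Outcomes). Seven further kinds of adverse event are listed as secondary safety outcomes.

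The go decision appears twice:

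- **Statistical Analyses:** the first condition, judged against control, is that "the treatment group did not have an increase in the incidence of adverse reactions". The second is that the arms have the same 90-day prognosis. If both hold, the programme goes on to phase 2.
- **Discussion, closing paragraph:** further trials are indicated if there is "no significant difference in the incidence of drug-related adverse events between the experimental group and the control group".

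The only comparison offered for event frequencies is a significance test at p < 0.05: a χ² test, or "Fisher exact-test, or continuity correction will be used where appropriate for comparison between the two groups". On size, Estimation of Sample Size says "our goal is to recruit 15 patients in each group", taken from rules of thumb for pilot studies, and adds: "The results of this study should be able to determine the initial safety and feasibility of intravenous infusion of C+P in AIS patients". No tolerable event rate, excess, confidence limit or event count is attached to the decision in any of these sections.

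**The concern.** The two statements differ in two ways. One asks for no increase and the other for no significant difference. One counts adverse reactions and the other counts drug-related adverse events. A result such as 3 events v 1 fails the first if read literally and passes the second.

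Neither is a sound basis for judging safety at this size. Non-significance with 15 v 15 mostly reflects low power, so a substantial excess can pass. A bar on any numerical excess errs the other way and often stops an infusion that adds no risk. The second condition, no difference in 90-day prognosis, is also stated without a margin.

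This rule is the decision that the trial exists to inform. The Discussion itself worries that the same dose given intravenously may interact more because of better bioavailability, so the rule needs to be able to respond to harm.

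**Working it through.** **Inputs.** 15 per arm (Estimation of Sample Size), 1:1 allocation (Randomization and Blindness), p < 0.05 (Statistical Analyses). Sidedness is not stated, so two-sided is assumed. The article gives no event rates, so all true rates below are assumptions. The sample size has no power, rate or margin behind it, so there is no figure to reproduce.

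**Step 1: what Fisher's test needs at 15 v 15.** With no control events and k treated events, the two-sided p is 2 × C(15,k)/C(30,k).

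- 4 v 0: 2 × 1365/27405 = 0.100, not significant.
- 5 v 0: 2 × 3003/142506 = 0.042, significant.
- With 1, 2 or 3 control events, the smallest significant treated counts are 7 (p = 0.035), 9 (p = 0.021) and 10.

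So 6/15 v 1/15 (40% v 7%, p = 0.080) would be reported as no significant difference.

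**Step 2: non-significance reading, one event type.** P(pass) = 1 − Σ Bin(a; 15, pT) × Bin(b; 15, pC), summed over all pairs with a > b and Fisher p < 0.05. For 20% v 0% this reduces to P(at most 4 events of 15 at 20%) = 1 − 0.164 = 0.836.

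| True rate, C+P v control | Passes (Fisher) | Passes (uncorrected χ²) |
|---|---|---|
| 20% v 0% | 83.6% | 64.8% |
| 20% v 5% | 91.7% | 81.2% |
| 30% v 10% | 85.1% | 72.3% |
| 30% v 5% | 72.5% | 55.4% |
| 40% v 10% | 67.5% | 49.0% |
| 40% v 5% | 48.1% | 30.5% |
| 50% v 10% | 46.4% | 27.4% |

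The last two rows show where the weakness ends: Fisher flags harms of that size in slightly more than half of trials.

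**Step 3: literal reading, hypotension alone, equal true rates.** By symmetry, P(treated count > control count) = (1 − P(tie))/2.

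- 5% in both arms: (1 − 0.368)/2 = 0.316.
- 10% in both arms: (1 − 0.250)/2 = 0.375.

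A harmless infusion is therefore stopped in 32% to 38% of trials. On this reading a harmful one is usually stopped too: 20% v 0%, 30% v 5% and 40% v 10% each show a numerical excess in about 96% of trials. The two readings thus lead to opposite decisions in the same scenarios.

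**Step 4: what 15 treated patients can exclude.** The exact one-sided 95% upper limit for 0/15 is 1 − 0.05^(1/15) = 18%. For 1/15, 2/15 and 3/15 the Clopper-Pearson limits are 28%, 36% and 44%.

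**The case against.** **This is a pilot, and it says so.** The claim is about initial safety, the Discussion concedes that a small sample may give spurious results, a go leads only to phase 2, and an independent physician monitors participants. All of that stands, and it rules out saying that the article claims proof of safety. A small pilot is acceptable. The defect is the stated inference, which the caveats do not change.

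**A reader might infer that a clearly harmful infusion would usually reach phase 2.** The documents do not support that as a general statement. It needs the Discussion's wording, since the literal wording under Statistical Analyses would usually stop such an infusion. It depends on assumed rates and fails for the largest harms. The pass rates also describe one binary event, not the whole rule: other listed events or the 90-day condition could block a go.

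**A reader might infer that the permitted tests contradict one another, citing 4/15 v 0/15.** Uncorrected χ² gives p = 0.032 there, against 0.100 (Fisher) and 0.107 (continuity-corrected). But the expected count is 2 per arm, so the uncorrected test would not ordinarily count as appropriate, and the other two agree.

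**A reader might infer that some listed event will almost always be higher on C+P.** A figure above 95% for at least one of eight event types needs independence and a rate of 5% or more for every type. At 2% each it is 83%, and the documents give no rates.

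**Conclusion.** The concern holds in this form: the article gives two go rules that must be reconciled, and neither can carry the safety decision at 15 v 15. Under non-significance by Fisher, excesses of about 15 to 30 percentage points on one event type pass in roughly two thirds to nine tenths of the scenarios tabulated, and only larger harms are flagged more often than not. Under no numerical excess, a harmless infusion is stopped in about a third of trials or more on hypotension alone.

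These sizes rest on assumed event rates, a two-sided 0.05 level and 15 per arm. If the n = 30 in the randomisation section meant 30 per arm, 20% v 5% would still pass in 76% of trials and 30% v 10% in 63% (Fisher). The qualitative conclusion does not depend on any single rate.

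**What to change.** 1. Replace the statements under Statistical Analyses and in the Discussion with one rule on one named event set, with hypotension requiring intervention as the main parameter. Remove non-significance as the criterion for safety.
2. Report the rate in each arm and the risk difference with exact or score confidence intervals. Base the go decision on these, against a tolerable rate, excess or event count that the sponsor's clinicians set before enrolment. Tabulate the pass probabilities of that rule at 15 per arm before adopting it.
3. State the 90-day condition in the same way, as an estimate with an interval and a stated margin.
4. Use the upper limits of 18%, 28%, 36% and 44% (0 to 3 events of 15) for reporting, not as a mandatory gate. A gate on the C+P arm alone ignores the control arm, and nothing can pass if the named limit is below 18%. With a purely illustrative limit of 20%, only 0/15 passes, so a true 5% rate would be stopped in 1 − 0.95^15 = 54% of trials.
5. Name Fisher's exact test as the supporting test.
6. Reword Estimation of Sample Size to say that the study will estimate initial safety, and that with 15 treated patients an event rate of up to about 18% cannot be excluded even if no event occurs.

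The cost is wording in three places. The rewording itself needs no extra patients, but the stated claim becomes less favourable, and the check in item 2 may show that a strict limit cannot be met with 15 treated patients.
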